**Abdominal circumference**										
Week	Mean	10% Centile	5% Centile	CV	%SE_50	%SE_10	%SE_5	Width_50	Width_10	Width_5
20	147.7	133.5	128.8	7.9	0.79	1.07	1.21	2.33	2.85	3.12
24	190.7	173.8	166.6	7.4	0.74	1.00	1.14	2.82	3.47	3.78
28	235.2	215.4	210.6	6.4	0.64	0.86	0.98	3.01	3.72	4.13
32	278.6	255.8	248.3	6.5	0.65	0.88	1.00	3.62	4.49	4.95
36	314.5	288.0	277.9	7.1	0.71	0.96	1.09	4.47	5.52	6.05
**Biparietal diameter**										
Week	Mean	10% Centile	5% Centile	CV	%SE_50	%SE_10	%SE_5	Width_50	Width_10	Width_5
20	46.7	44.0	42.0	5.6	0.56	0.76	0.86	0.52	0.67	0.72
24	59.0	56.0	55.0	4.8	0.48	0.65	0.74	0.57	0.73	0.81
28	70.8	68.0	67.0	3.9	0.39	0.53	0.60	0.55	0.72	0.80
32	80.1	77.0	75.0	3.7	0.37	0.50	0.57	0.59	0.77	0.85
36	87.1	83.0	81.0	3.7	0.37	0.50	0.57	0.64	0.83	0.92
**Head circumference**										
Week	Mean	10% Centile	5% Centile	CV	%SE_50	%SE_10	%SE_5	Width_50	Width_10	Width_5
20	177.4	164.4	161.2	5.8	0.58	0.78	0.89	2.06	2.57	2.87
24	225.0	212.3	209.2	4.9	0.49	0.66	0.75	2.21	2.81	3.14
28	269.4	254.9	251.8	4.3	0.43	0.58	0.66	2.32	2.96	3.32
32	302.8	286.9	281.6	4.1	0.41	0.55	0.63	2.48	3.17	3.54
36	325.1	308.1	300.1	4.1	0.41	0.55	0.63	2.67	3.41	3.77
**Femur length**										
Week	Mean	10% Centile	5% Centile	CV	%SE_50	%SE_10	%SE_5	Width_50	Width_10	Width_5
20	32.6	30.0	29.0	6.9	0.69	0.93	1.06	0.45	0.56	0.61
24	43.2	41.0	40.0	4.7	0.47	0.63	0.72	0.41	0.52	0.58
28	53.0	51.0	50.0	3.7	0.37	0.50	0.57	0.39	0.51	0.57
32	61.9	59.0	58.0	3.3	0.33	0.45	0.51	0.41	0.53	0.59
36	69.3	67.0	65.0	3.2	0.32	0.43	0.49	0.44	0.58	0.64
**Humerus length**										
Week	Mean	10% Centile	5% Centile	CV	%SE_50	%SE_10	%SE_5	Width_50	Width_10	Width_5
20	31.4	28.0	27.0	8.9	0.89	1.20	1.37	0.56	0.67	0.74
24	40.7	38.0	37.0	6.8	0.68	0.92	1.04	0.55	0.70	0.77
28	48.6	45.0	44.0	6.3	0.63	0.85	0.97	0.61	0.77	0.85
32	55.7	52.0	51.0	5.7	0.57	0.77	0.87	0.63	0.80	0.89
36	61.2	57.0	56.0	5.4	0.54	0.73	0.83	0.66	0.83	0.93

The following table lists, for every biometrical parameter, the number of subjects needed to detect as statistically significant the smallest meaningful difference d with type I error rate of 0.05 and a power of 0.80 with values of variance (σ^2^) and correlation (ρ^2^) as estimated using the data from the WHO randomized trial of calcium supplementation in low intake women [37]. The presented sample sizes have been calculated by applying the formula:

$$m=\frac{2{\left(z_{\alpha }+z_{Q}\right)}^{2}\sigma^{2}\left(1-\rho \right)}{ns_{x}^{2}d^{2}}$$

Where d is the minimum difference in the rate of change per unit time (week) in the five biometrical parameters by centre, n is the number of visits (n = 8) and $s_{x}^{2}$ is the within subject variance [38]. The values of d shown in Table 3 indicate that the sample size needed for the level of precision requested will be very conservative to detect differences in the rate of change between centres.

**Table 3 T3:** Estimated sample size and computation assumptions for biometrical parameters

**Biometrical parameter**	**Sample size**	**Variance**	**Rho**	**d (mm)**
Biparietal Diameter	32	10.2	0.34	0.1
Head circumference	23	174	0.28	0.5
Abdominal circumference	28	263	0.43	0.5
Femur length	16	5	0.32	0.1
Humerus length	35	11	0.32	0.1

### Data management

Data will be collected *via* an internet based data management system as done with other WHO coordinated studies. The online data collection system will allow for real time solutions of queries or other problems in data collection, such as missing or non-valid data as well as for online checking of images by the international coordination unit.

All data will be stored in a GCP compliant server, and data transmission will be encrypted to assure data integrity and patient confidentiality. Access to the data management web system will be password protected and only authorized users will have access. Data changes will be documented. The system will maintain an audit trail, data trail and edit trail as well as back up of the data.

Data entered into the web system will be checked by the coordinating unit at WHO for completeness, accuracy, reliability and consistent intended performance. The data management team will be responsible for generating the interim and final data report.

These procedures have been used in previous HRP multi-centre trials and proven to be efficient and compliant with the HRP/WHO Standard Operating Procedures as well as with the 21 CFR Part 11 of the Code of Federal Regulations that deals with the United States Food and Drug Administration (FDA) guidelines on electronic records.

### Data analysis

Population percentiles will be calculated by applying polynomial regression methods, using the generalized estimating equations method, to model the mean at specific gestational ages, taking into account correlations between repeated measurements on the same subjects [38]. To estimate the standard deviations at each gestational age, we will use the method of the absolute residuals proposed by Altman [39]. This methodology takes into account the increase in variance with advancing gestation typical of fetal biometry data [39]. Differences in linear growth among populations of different geographical origin (categorized by study site) will be tested by evaluating the proportion of total variability in fetal biometrical measurements attributable to sites and individuals, as well as differences among sites and the effect of excluding sites on the percentiles of the total sample, as done in the MGRS [40]. The same procedure will be used to test for differences in growth related to the sex of the fetus.

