### Sample size

The total sample size will be 1400 pregnant women and their infants. Each country centre will collect data from 140 women. This number is sufficient for the development of local centile growth charts with a high level of precision, accounting for exclusions to final analysis due to inability to follow up and occurrence of pregnancy complications [34,35].

The sample size needed for the estimation of a specific percentile was computed using the following formula [36]:

$$n=\frac{\left(1+z_{\alpha }^{2}/2\right)}{{\left(\frac{\%\mathrm{SE}\;P_{\alpha }}{\%\mathrm{CV}}\right)}^{2}}$$

where z_α_ is the standard normal deviation corresponding to the percentile being estimated, % SE C_α_ is the expected percentage standard error of the percentile and % CV is the percentage coefficient of variation. Sample sizes were computed for 5 different parameters (biparietal diameter, abdominal and head circumference and femur and humerus length) and for 3 different percentiles: 5%, 10% and 50%. Information about the coefficient of variation was obtained from data on serial ultrasonographic examination conducted on approximately 500 pregnancies in the context of the WHO randomized trial of calcium supplementation in low intake women [37]. Additionally, the expected half-width of the confidence interval with a sample size n = 100 was computed.

Table 2 shows the levels of precision obtainable with a sample size of 100 women for various biometrical parameters. In addition the proposed sample size of 140 women per centre will allow for testing for differences in growth patterns across centres [38].

**Table 2 T2:** Levels of precision obtained with a sample size of 100 women for some biometrical fetal parameters (values and half widths in mm)

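### The named centile method relies on normality at each gestational age, and the protocol's own planning data suggest this may not hold in the lower tail of head circumference

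*Protocol article*

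**What the plan says.** The Data analysis section of the protocol article gives the only description of how the charts will be built. For the mean: "Population percentiles will be calculated by applying polynomial regression methods, using the generalized estimating equations method, to model the mean at specific gestational ages". For the spread: "To estimate the standard deviations at each gestational age, we will use the method of the absolute residuals". The section presents the second step as a way to let variance grow with gestation. It mentions no transformation or skewness term.

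The Sample size section uses a precision formula in which z "is the standard normal deviation corresponding to the percentile being estimated". That formula serves planning and is not the centile method, but it shows the same normal-theory thinking.

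The inputs to that formula are in Table 2, which lists mean, 10th centile, 5th centile and CV by week for five parameters. On their origin the section says: "Information about the coefficient of variation was obtained from data on serial ultrasonographic examination conducted on approximately 500 pregnancies". The source was a trial of calcium supplementation in women with low intake. The number of scans at each week is not given.

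**The concern.** The outer centiles are the study's product: charts intended for international use, against which small fetuses will be identified. A mean curve and an SD curve fix a 5th centile only once a shape is assumed. Scaling absolute residuals to an SD also uses a normal-theory constant. If the lower tail is shorter than normal at one gestation and longer at another, a single normal multiplier errs in opposite directions. The true share below the nominal 5th centile would then change with gestation for reasons unrelated to growth. Recruiting more women does not remove that error.

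Table 2 prints the mean, the spread and the lower centiles side by side. Its centiles do not equal mean − z × SD, and for biparietal diameter, femur length and humerus length they are whole millimetres. They therefore look like observed values that can be set against the normal prediction.

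**Working it through.** **Inputs** (Table 2, HC; mm and %). The rows for weeks 20 and 24 read "20 177.4 164.4 161.2 5.8" and "24 225.0 212.3 209.2 4.9" (week, mean, 10th centile, 5th centile, CV). The others are: week 28, 269.4, 254.9, 251.8, 4.3; week 32, 302.8, 286.9, 281.6, 4.1; week 36, 325.1, 308.1, 300.1, 4.1.

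**Step 1: reproduce the plan's own figures.** %SE = CV × √((1 + z²/2)/n), with n = 100 and z = 1.645, so 1 + z²/2 = 2.353.
- Week 24: 4.9 × √0.02353 = 0.75%; half-width 2 × 0.752% × 209.2 = 3.14 mm.
- Week 36: 4.1 × √0.02353 = 0.63%; half-width 2 × 0.629% × 300.1 = 3.77 mm.

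Both agree with Table 2, as do the table's other %SE values and half-widths. The columns are therefore being read correctly.

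**Step 2: compare the printed 5th centile with normal theory.** SD = mean × CV; normal limit = mean − 1.645 × SD.

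| Week | SD | (Mean − 5th)/SD | Normal limit | Printed 5th | Difference |
|---|---|---|---|---|---|
| 20 | 10.29 | 1.57 | 160.5 | 161.2 | −0.7 |
| 24 | 11.03 | 1.43 | 206.9 | 209.2 | −2.3 |
| 28 | 11.58 | 1.52 | 250.4 | 251.8 | −1.5 |
| 32 | 12.41 | 1.71 | 282.4 | 281.6 | +0.8 |
| 36 | 13.33 | 1.88 | 303.2 | 300.1 | +3.1 |

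Rounding of the CV (±0.05) moves the week 24 and 36 limits by only 0.2–0.3 mm.

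**Step 3: share below the normal limit.** A straight line on the probit scale through the printed 5th and 10th centiles gives 4.2%, 2.75%, 3.5%, 5.6% and 6.6% at weeks 20 to 36.
- Week 36: the limit lies between the two printed centiles, so this is interpolation. A line linear in probability gives 5 + 5 × 3.08/8.0 = 6.9%; an exponential tail gives 5 × 2^(3.08/8.0) = 6.5%.
- Week 24: the limit lies below the lowest printed centile, so this is extrapolation. The linear version gives 5 − 5 × 2.33/3.1 = 1.2%; the exponential version gives 5 × 2^(−2.33/3.1) = 3.0%.

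**Step 4: could this be chance?** In simulated normal data with five independent weeks, the 5th centile in SD units ranged by at least 0.44 (1.876 − 1.433 = 0.443) with probability about 0.14 at 100 scans per week, 0.04 at 150, 0.014 at 200 and 0.002 at 300. Using the range allows for picking the extreme weeks afterwards. The numbers per week are assumptions.

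**Step 5: other parameters and the 10th centile.** AC, also printed to 0.1 mm, has its 5th centile 1.62 to 1.71 SD below the mean, with 4.8–5.5% below the normal limit at every week. The HC 10th centile is within 0.35 mm of normal theory at weeks 20, 28, 32 and 36, and 1.4 mm off at week 24. The whole-millimetre centiles of the other three parameters are too coarse to settle the matter.

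**Step 6: scale.** With 1,000 analysable women (assumed: 100 at each of ten centres), the half-width of a normal-theory HC 5th centile at week 36 is about 2 × 13.33 × √(2.353/1000) = 1.3 mm. A shape error of 3.1 mm, if it carried over to the study, would be about 2.4 times that.

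**The case against.** The strongest objection is that the criticised rule is not printed. The article does not say that centiles are mean ± z × SD on the untransformed scale, and a condensed article may leave the scale and the fit checks to a full protocol or analysis plan that is not shown. This stands in part: the absence of a check is not in itself the finding. What remains is that the method the article does name depends on shape, and its own planning figures cast some doubt on the shape for one parameter.

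The second objection concerns the strength of the evidence. A reader might infer that Table 2 shows a non-normal HC tail and that the charts would flag 2.8% at week 24 and 6.6% at week 36. The documents do not support that. The roughly 500 pregnancies are a total, not a count per week, and at about 100 scans per week the pattern is compatible with chance. The week 24 figure is an extrapolation. AC fits normality, and the HC 10th centile mostly does, so at week 36 the evidence is a single sample quantile. Outliers or a spread of gestational ages within a week could also have widened the CV.

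Third, the planning women came from a different population. This study selects prescriptively, requires CRL and LMP dating to agree within 7 days, and ends participation when serious illness leads to growth restriction. Such selection may shorten a long lower tail near term. This also stands, so the ratio of 2.4 is conditional and is not an estimate of bias in the study.

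None of this shows that normality holds for HC. It makes the case for checking the assumption rather than abandoning the method in advance.

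**Conclusion.** The point holds in a limited form, as an inexpensive improvement. On the natural reading, the outer centiles rest on normality at each gestational age, and the planning data suggest this may fail in the HC lower tail. The printed 5th centile moves from 1.43 to 1.88 SD below the mean between weeks 24 and 36. For a nominal 5%, the share flagged could be about 6.6% at week 36 and, illustratively, 3% or less at week 24.

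This rests on three assumptions: that the printed centiles are observed values, that substantially more than 100 scans per week lie behind them, and that the shape carries over at least in part to the prescriptive sample. The documents confirm none of these. They support a check with a fallback fixed in advance, not a claim that the planned charts are miscalibrated.

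**What to change.** Amend the Data analysis section as follows.

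- Keep the polynomial mean and the absolute-residual SD as the starting model.
- For each parameter and gestational-age band, compare the observed share below the fitted 5th, 10th, 90th and 95th centiles with the nominal share.
- State a tolerance that allows for sampling error and repeated measures, for example whether the nominal share lies within a 95% interval from a bootstrap that resamples women. Without a tolerance the check would trigger on noise.
- Where a parameter fails, derive its centiles from a model with gestational-age-dependent skewness (LMS / Box-Cox) or from quantile regression, instead of mean ± z × SD.

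The cost is analysis wording and some extra modelling on the same data. Outer centiles become less precise where the fallback is used. For quantile regression under normality, the variance factor p(1 − p)/φ(z)² is 4.47 at the 5th centile against 2.353, so the SE is up to √(4.47/2.353) = 1.38 times as large. For HC at week 36 with 1,000 women, the half-width would rise from about 1.3 to 1.8 mm.

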## Discussion

The data from this study, if findings are similar across diverse populations, may facilitate the adoption of an universal growth standard for international use. If heterogeneity by centre is detected despite selecting study populations according to the prescriptive approach, the study results will indicate the need to develop local/ethnically specific standards.

### Technical and ethical approvals

The protocol received technical and ethical approval from the WHO Research Project Review Panel (RP2) and Research Ethics Review Committee respectively as well as from appropriate national and institutional ethic review bodies as applicable for each study centre.

## Abbreviations

AC: Abdominal circumference; BMI: Body mass index; BPD: Biparietal diameter; CH: Chest; CRL: Crown rump length; CV: Coefficient of variation; EV: Endovaginal; FFL: Fetal foot length; FL: Femur length; GA: Gestational age; H: Head; HC: Head circumference; HL: Humerus length; ICC: Intraclass correlation coefficient; ISUOG: International Society for Ultrasound in Obstetrics and Gynaecology; IUGR: Intra uterine growth restriction; LA: Lower arm; LL: Lower leg; LMP: Last menstrual period; MDG: Millennium Development Goal; MGRS: Multi-centre Growth Reference Study; OFD: Occipito-frontal diameter; SE: Standard error; TCD: Trans cerebellar diameter; UA: Upper arm; LA: Lower arm; WHO: World Health Organization.
